#### 4. Need for help in daily life activities

Use will be made of the Barthel index [45] for the evaluation of basic daily life activities and of the Lawton and Brody index [46] for the evaluation of instrumental daily life activities. The short version informant test (IQCODE) will be applied [47,48]. This is a questionnaire to be completed by a relative or person close to the patient. Following a series of short instructions, and in very little time, the informant is asked to recall how the patient was 10 years ago, and how he or she has changed since then, based on a 5-point Likert scale. The short version comprises 17 questions.

#### 5. Neuropsychological assessment protocol

a) Cognitive screening: The Folstein Mini-Mental Test, MMSE [49], and the 7 Minute Screen [50,51], are cognitive screening tests that explore a number of cognitive areas which are particularly affected in an early stage in Alzheimer-type dementia and in other dementias.

b) Evaluation of the premorbid situation: The word accentuation test [52] allows us to quickly estimate the premorbid intellectual level of the subject. It consists of 30 infrequent words that are presented to the subject (without accentuations), and which he or she must read correctly (phonetic accent).

c) Attention-concentration: This is a digit subtest to the right and reverse [53]. It assesses attention, as well as storage and immediate recall of a series of numbers.

d) Speech: The Boston vocabulary test [54] explores denomination capacity based on the visual confrontation of 60 images.

Semantic - phonetic generation [55], comprising two subtests. The first, *names of animals*, evaluates semantic verbal fluency. The subject is asked to name animals as quickly as possible and in one minute. The score is the number of words evoked by the patient. The second subtest is *words that begin with the letter "p"*, and evaluates phonologic verbal fluency. The subject is asked to name words that begin with the letter "p". The score is the number of words evoked by the patient in a period of one minute.

e) Logical memory: Babcock story [56], immediate and delayed. The explorer reads a story to the subject, who in turn is required to recall it immediately, thereby assessing retention memory and immediate recall corresponding to logical structured verbal material. After non-mnesic interference (approximately 15 minutes), the subject is instructed to repeat what he or she remembers about the story (delayed logical verbal memory). The story consists of 21 information units.

f) Visuoconstruction memory: Rey complex figure test [57]. This test involves two phases: copy and memory. Memory reproduction informs us of the visual memory of the subject, as well as of his or her visuoconstruction capacity. Subject performance is evaluated according to the number of correct units conforming the complete figure (the maximum score being 36), the type of execution of the subject, and the time (in seconds) used to construct the figure.

h) Visual memory: The Benton visual retention test will be used [58]. We will apply form C, Administration A. This involves presentation of each of the sheets, during 10 seconds, followed by immediate memory reproduction or recall by the subject. This test evaluates the visuospatial perception of the subject, as well as visual memory, visuoconstruction skills and visual conceptualization. Subject performance is evaluated according to the number of correct reproductions (the maximum score being 10) and error assessment (taking into account the specific type of error made by the subject: omission, distortion, displacement, perseverance, rotation, size and whether located to left or right).

i) Executive function: Abbreviated Frontal Assessment Battery (FAB)[59]. This test evaluates frontal lobe functions based on 6 tasks: similarities (formation of concepts), verbal fluency (mental flexibility), motor series (programming), interference (execution of conflictive instructions), control (response inhibition) and autonomy (environmental independence). The action-verb fluency test [60] in turn requires the subject to evoke the largest possible number of words designating an action (verbs), in 60 seconds. The score in this task is the total number of words correctly evoked within the limited time interval.

g) Visuoconstruction skills: the Rey complex figure test [57]. Copying of the figure evaluates subject visual perception, practical-constructive skills, visuospatial analytical capacity, and right-left orientation. The assessment is the same as commented above in the memory figure reproduction phase.

h) Cognitive impairment: classification of the severity of cognitive impairment in 7 global stages ranging from normal to severe impairment, based on the Global Deterioration Scale (GDS) [61].

### Procedure

All participants will be informed of the purpose of the study by telephone and conventional mail, and will be asked to give written informed consent to participation. Once consent has been obtained, all subjects will receive a card stating the place, date and exact time of the evaluation. One day before the study the subjects will be telephoned to remind them of the appointment. Evaluation will be carried out in the Faculty of Psychology of the University of Salamanca, in Room 19 (specifically used for neuropsychological tests).

The sessions will be individualized, and the procedure will be the same for all participants, using the aforementioned measurement instruments.

The estimated duration of the evaluation is 120 minutes, with two resting intervals of about 15 minutes each.

The clinical and laboratory test data can be collected on occasion of a second interview to be arranged with the participants and/or relatives.

### Statistical analysis

A descriptive analysis of the data will be made, establishing comparisons with the baseline evaluation of the previous study. Posteriorly, an analysis will be made of the qualitative variables using the chi-squared test, and the qualitative and quantitative variables will be analyzed using the Student t-test and analysis of variance (ANOVA), depending on whether two or more categories are involved. An analysis will be made of the correlations of the quantitative variables, together with multiple regression analysis to identify the variables associated with cognitive impairment diagnosed by the neuropsychological tests.

Likewise, an evaluation will be made of the sensitivity, specificity and predictive values of the tests employed in screening for cognitive impairment, using the neuropsychological evaluation made as gold standard.

Lastly, we will analyze the evolution of the different parameters between the two evaluations made, attempting to identify those variables with greater predictive capacity in reference to the evolution of cognitive impairment.

The information will be analyzed according to the place of residency, age and sex of the patient, the family situation and patient cognitive impairment, risk factors and comorbidity index.

Data input will be made using the Teleform system, with a questionnaire previously designed for the project, and exporting the data to the SPSS statistical package for posterior analysis.

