Less than one-half of all patients with Alzheimer's disease have been diagnosed, and of these subjects, approximately 25% are receiving some kind of treatment [43]. The number of individuals with undiagnosed cognitive impairment is therefore expected to be high, particularly in groups with certain risk factors. One of the factors explaining why many people with cognitive impairment have not been diagnosed is related to the fact that we have no cognitive impairment screening tool in the elderly population sufficiently warranted by the scientific community and the professionals who care for such patients.

Based on a neuropsychological battery especially adapted for the study of elderly people, we will carry out a study of cognitive performance in people over 65 years of age in Salamanca (Spain), with special emphasis on the identification of early symptoms of cognitive impairment, with the purpose of detecting mild cognitive impairment and of studying the relationships between this clinical situation and cardiovascular risk factors.

The following objectives have been established:

1. To study the cognitive performance of people over 65 years of age in Salamanca, with a view to estimating the prevalence of the different manifestations of cognitive impairment and its severity.

2. To analyze the association of cardiovascular risk factors (diabetes, arterial hypertension, dyslipidemia and metabolic syndrome) in patients over age 65 with mild cognitive impairment.

3. To use the Mini - Mental State Examination (MMSE) and the 7 Minute Screen test as screening tools for cognitive impairment in the elderly population under study.

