### Measurements

The principal study measurements are the following:

a) Sociodemographic variables: age, sex, educational level, marital status, family unit.

b) Anthropometric variables and physical evaluation: body weight, height, waist circumference, blood pressure, heart rate, physical activity, lipid profile, blood glucose.

c) Vascular risk factors: smoking, hypertension, diabetes mellitus, dyslipidemia, obesity, alcohol intake.

d) Cardiovascular disease: stroke, heart disease, neuropathy, retinopathy.

e) Drug use (antihypertensive, antidiabetic, lipid-lowering and antiplatelet drugs, psychoactive medication).

f) Comorbidity.

g) Functional grade will be evaluated in reference to daily life activities (both basic and instrumental), and data from an informant will be obtained.

h) Neuropsychological assessment: assessment of the premorbid situation, attention-concentration, speech, logical memory, auditory-verbal learning, visioconstruction memory, visual memory, executive function. Following evaluation, the impairment phases will be classified, ranging from normality to the most severe phases of dementia.

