## Discussion

There are studies in which a link has been established between cardiovascular risk factors and the development of dementia. However, few studies have related mild cognitive impairment to cardiovascular risk. We hope that this study will afford objective information on the representative prevalence of mild cognitive impairment in the population over 65 years of age in Salamanca.

We will conduct an analysis of the cardiovascular risk factors in the selected sample, allowing us to establish the possible correlation between certain cardiovascular risk markers and mild cognitive impairment. If found, such a correlation would be very useful for future studies designed to allow a certain prevention of such impairment, based on control of the cardiovascular risk factors.

The results obtained moreover will allow us to assess the predictive capacity in detecting cognitive impairment from the applied screening tests (MMSE and 7 Minute Screen), since their results will be contrasted with those of the detailed neuropsychological explorations. The importance of the early detection of cognitive impairment should be stressed, since it will allow the start of adequate treatment and thus can contribute to improve patient quality of life.

Lastly, we wish to point out that since a randomized population-based sample from the city of Salamanca is involved, the information obtained may be of increased representativeness - particularly considering that many studies suffer bias due to the lack of purely randomized criteria in selecting the participants.

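### One pooled sensitivity and PPV for the MMSE and 7 Minute Screen across all stages of impairment would not support conclusions about early detection; add stage-specific estimates and estimates without previously diagnosed dementia

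*Protocol article*

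**What the plan says.** Objective 3 (Background) is to use the MMSE and the 7 Minute Screen "as screening tools for cognitive impairment in the elderly population under study". For this the Statistical analysis section plans that "an evaluation will be made of the sensitivity, specificity and predictive values of the tests employed in screening for cognitive impairment". The reference is the full battery; the section describes this step as "using the neuropsychological evaluation made as gold standard". It names no stage restriction, no separate estimate for mild impairment and no Global Deterioration Scale (GDS) cut.

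The reference classification covers the whole range. Under Measurements, "the impairment phases will be classified, ranging from normality to the most severe phases of dementia". The neuropsychological protocol uses the GDS for "classification of the severity of cognitive impairment in 7 global stages ranging from normal to severe impairment". The Design section states no exclusion for known dementia, and under Procedure everyone is assessed in the same way. Dementia is one of the listed comorbidity items.

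The stated emphasis is narrower. The Background describes the work as being "with special emphasis on the identification of early symptoms of cognitive impairment, with the purpose of detecting mild cognitive impairment", expects many undiagnosed cases, and says that "we have no cognitive impairment screening tool in the elderly population sufficiently warranted by the scientific community". After announcing the comparison of the screens with the full battery, the Discussion states: "The importance of the early detection of cognitive impairment should be stressed, since it will allow the start of adequate treatment".

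**The concern.** The planned estimate and the conclusion to be drawn from it concern different groups. Sensitivity computed over all impaired participants is an average over stages, weighted by how many people at each stage attend. If brief tests find dementia more easily than mild impairment, the average is pulled up by people whose impairment is plain, some of whom may already have a diagnosis. The Abstract says the study will establish how useful the screens are. A reader would naturally carry the pooled sensitivity and PPV over to early detection, where performance may be clearly worse. The problem would remain even with a reference standard wholly independent of the screens.

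**Working it through.** **What the sample size was built on.** The Power analysis takes 16% for mild impairment plus dementia, with 4 points of precision and a population of 34,020.

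- n0 = 1.96² × 0.16 × 0.84 / 0.04² = 322.7
- With finite population correction: 322.7 / (1 + 321.7/34,020) = 319.7, so 320, as stated.

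The study was therefore sized on the pooled category. The article gives no sample size for the accuracy objective and no sensitivity or specificity for either test.

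**Share of dementia among impaired participants.** The Background gives dementia prevalences of 6.4% (regional, 65 and over) and 8% (over 65).

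- 6.4/16 = 40%; 8/16 = 50%
- Among the 327 people in the Design section: 0.16 × 327 ≈ 52 impaired, of whom 21–26 have dementia and 26–31 mild impairment.

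**Sensitivity.** Pooled Se = share × Se(dementia) + (1 − share) × Se(mild), so the gap is

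pooled Se − Se(mild) = share × [Se(dementia) − Se(mild)].

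Assumptions, not from the article: Se(mild) 0.40–0.70 and Se(dementia) 0.85–0.95. The bracket then runs from 0.85 − 0.70 = 0.15 to 0.95 − 0.40 = 0.55.

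| Dementia share of impaired | Smallest gap (points) | Largest gap (points) |
|---|---|---|
| 12.5% (2% of an unchanged 16%) | 1.9 | 6.9 |
| 40% | 6.0 | 22.0 |
| 50% | 7.5 | 27.5 |

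The first row represents poor attendance by people with dementia. If mild impairment instead stays at 9.6% or 8% and dementia falls to 2%, the share is 2/11.6 = 17% or 2/10 = 20%. The gap is then 2.6 to 11.0 points.

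**All four measures, one example.** Assume Se(mild) 0.50, Se(dementia) 0.90, specificity 0.85, and dementia 6.4%. Per person sampled, false positives are 0.84 × 0.15 = 0.126 and true negatives are 0.84 × 0.85 = 0.714.

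| | Pooled | Mild vs normal |
|---|---|---|
| Sensitivity | 0.4 × 0.90 + 0.6 × 0.50 = 0.66 | 0.50 |
| Specificity | 0.85 | 0.85 |
| PPV | 0.1056/(0.1056 + 0.126) = 0.456 | 0.048/(0.048 + 0.126) = 0.276 |
| NPV | 0.714/(0.714 + 0.0544) = 0.929 | 0.714/(0.714 + 0.048) = 0.937 |

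Much of the PPV difference is prevalence. Sensitivity 0.66 with dementia cases removed would give 0.0634/(0.0634 + 0.126) = 0.335. The fall from 0.456 to 0.335 is thus due to prevalence, and only the rest, to 0.276, to lower sensitivity.

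Specificity uses only unimpaired people, so it cannot change as long as mild impairment counts as impaired. Removing dementia cases leaves true negatives as they are and can only reduce false negatives, so pooled NPV is never higher than NPV for mild impairment versus normal.

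**Removing only previously diagnosed dementia.** Assume half the dementia cases were already diagnosed, with the same 0.50 and 0.90.

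- Dementia 6.4%: (0.032 × 0.90 + 0.096 × 0.50)/0.128 = 0.60, against 0.66 pooled.
- Dementia 8%: (0.04 × 0.90 + 0.08 × 0.50)/0.12 = 0.63, against 0.70 pooled.

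**Precision.** Approximate 95% half-widths for sensitivity, 1.96 × √[Se(1 − Se)/n]:

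- Pooled, 52 cases, Se 0.66: 0.13
- Without prior diagnosis, 39–42 cases, Se 0.60–0.63: 0.15
- Mild only, 26–31 cases, Se 0.50: 0.18–0.19

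**The case against.** **Pooling is inferred.** The article states neither a cut nor a pooling rule, and it condenses a fuller protocol that may hold both. The Statistical analysis section also says results will be broken down by several factors, cognitive impairment among them. This is fair, and a missing GDS cut alone would be no finding. But objective 2 specifies mild impairment while objective 3 does not, the Power analysis adds mild impairment and dementia together, and the staging runs to severe. A single all-stage estimate is the plain reading, and the general sentence on breakdowns does not promise accuracy by stage.

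**The pooled estimate answers objective 3.** This stands. The objective concerns impairment in general in the population studied. Undiagnosed dementia is also a proper screening target: the Background says fewer than half of people with Alzheimer's disease have been diagnosed. So mild versus normal should not replace the pooled result.

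**People with dementia may not attend.** The assessment takes 120 minutes at a university faculty, and the Methodological limitations name mental impairment as a main cause of loss. This stands as to size: the gap may be only a few points. It also means that the pooled figure depends on who attends, which is itself a reason to report by stage.

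**Sampling error is larger than some of the effect.** Removing only previously diagnosed dementia moves sensitivity by about 6–7 points in the example, against a half-width of about 15. That is true. But the shift is systematic in direction, and an interval around the pooled figure does not reveal it.

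**Conclusion.** The point holds in a limited form. As worded, the plan yields one sensitivity and one PPV per test across all stages, while the study's emphasis is on early and undiagnosed impairment. If the tests detect dementia better than mild impairment, those two figures are likely to overstate performance for mild impairment. Under the assumed accuracies the sensitivity gap is about 2 to 27.5 points. The upper part of that range needs dementia to make up 40–50% of impaired participants, which follows from the article's prevalences but may not hold among attenders.

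A reader might infer more than the article supports:

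- That all four measures are inflated. Specificity is unchanged if mild impairment counts as impaired, and NPV is, if anything, slightly understated.
- That overstatement is certain and large. The article gives no test accuracies, and attendance could make the gap small.
- That the pooled analysis is wrong. It is valid for objective 3 as written; what it does not support is a claim about early detection.

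**What to change.** Keep the pooled accuracy estimate for objective 3. State which GDS stages count as impaired and which as mild, and specify before analysis:

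1. Sensitivity, specificity and predictive values in participants without a dementia diagnosis made before the study evaluation. Dementia first found by the study stays in as a target condition.
2. Sensitivity and predictive values for mild impairment versus normal, by GDS stage.
3. Confidence intervals for all of these.

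Base any statement on usefulness for early detection on items 1 and 2.

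GDS stage and clinical history are already to be collected. The article does not say whether the comorbidity item for dementia reflects a diagnosis made before the study or the study's own assessment, so the source and timing of the diagnosis should be recorded.

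The cost is precision and a less favourable headline. With about 26–31 mild cases among 327 participants, the half-width for sensitivity is near 0.18–0.19, against about 0.13 pooled. If the 420 people in the Abstract are assessed, there would be about 34–40 mild cases (420 × 0.08 and 420 × 0.096).

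### The gold standard for the MMSE and 7 Minute Screen is not kept separate from those two tests, so their accuracy may be overstated

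*Protocol article*

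**What the plan says.** All references are to the protocol article.

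- **Objective 3 (end of Background):** "To use the Mini - Mental State Examination (MMSE) and the 7 Minute Screen test as screening tools for cognitive impairment".
- **Statistical analysis:** "an evaluation will be made of the sensitivity, specificity and predictive values of the tests employed in screening for cognitive impairment", and this is done "using the neuropsychological evaluation made as gold standard".
- **Measurement instruments, "5. Neuropsychological assessment protocol":** the first entry is "a) Cognitive screening: The Folstein Mini-Mental Test, MMSE [49], and the 7 Minute Screen [50,51], are cognitive screening tests". The last entry of the same section is the "classification of the severity of cognitive impairment in 7 global stages ranging from normal to severe impairment, based on the Global Deterioration Scale".
- **Measurements, item (h):** the assessment is described by domain, without naming either screen. The item closes with "Following evaluation, the impairment phases will be classified, ranging from normality to the most severe phases of dementia".
- **Procedure:** sessions are individual, and "the procedure will be the same for all participants, using the aforementioned measurement instruments".
- **Discussion:** the results of the two screens are to be set against the in-depth neuropsychological examination.

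The article does not say which scores determine the GDS stage, who assigns it, or whether that person knows the screen results.

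**The concern.** A diagnostic accuracy estimate needs a reference that does not depend on the index test. Here the reference is named by a broad term, and the section that describes what the term covers puts both index tests first. Read literally, the MMSE and 7 Minute Screen help to decide who counts as impaired and are then scored on how well they agree with that decision (incorporation bias). Even if no formula uses them, a global stage assigned by someone who has seen the screen scores can be drawn towards them (review bias).

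The abstract and the Discussion both promise a conclusion on how useful the two tests are. If part of the agreement is built in, the reported figures would not show what the tests achieve against an independent work-up.

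This is more than detail that an article leaves to the full protocol. The article itself names the reference standard and describes its content, and the two do not clearly exclude the tests under evaluation.

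**Working it through.** **Step 1: the text side by side.** The article states no sensitivity, specificity, predictive value or cut-off, so there is no figure to reproduce. The question is whether the screens lie inside or outside the reference.

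| Place | Points to |
|---|---|
| Instrument section 5: screens are item (a), GDS staging is the last item | inside |
| Statistical analysis: the whole neuropsychological evaluation is the gold standard, with no exclusion | inside, if read with section 5 |
| Measurements (h): domain list without the screens, then staging | outside |
| Discussion: screens set against the in-depth examination | outside |

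The list in Measurements (h) is not a full definition. It omits visuoconstruction skills, which have their own entry in section 5, and it names auditory-verbal learning, which has none. It therefore does not settle which tests feed the stage.

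**Step 2: direction and possible size.** This is an illustration. Only the first input comes from the document.

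- Impaired: 16% (Power analysis, mild cognitive impairment plus dementia).
- Screen-positive: 20% (assumed).
- One underlying ability. Reliability, meaning squared correlation with that ability, is 0.60 for the screen S and 0.75 for the rest of the battery B (assumed).
- Standardised normal scores, with reference score R = (1 − w)B + wS. The weight w of the screen is 0, 0.1, 0.2 or 0.3 (assumed). The worst 16% on R count as impaired.

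Correlation of S with B: r = √(0.60 × 0.75) = 0.671.

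Correlation of S with R: ρ = [(1 − w)r + w] / √[(1 − w)² + w² + 2w(1 − w)r]. For w = 0.1: (0.9 × 0.671 + 0.1) / √(0.81 + 0.01 + 0.18 × 0.671) = 0.704 / 0.970 = 0.726.

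Let J be the bivariate normal proportion that is both screen-positive and impaired. Then sensitivity = J/0.16, specificity = 1 − (0.20 − J)/0.84, PPV = J/0.20 and NPV = 1 − (0.16 − J)/0.80.

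| Reference | ρ | J | Sensitivity | Specificity | PPV | NPV |
|---|---|---|---|---|---|---|
| w = 0 | 0.671 | 0.0935 | 58% | 87% | 47% | 92% |
| w = 0.1 | 0.726 | 0.1008 | 63% | 88% | 50% | 93% |
| w = 0.2 | 0.779 | 0.1086 | 68% | 89% | 54% | 94% |
| w = 0.3 | 0.829 | 0.1168 | 73% | 90% | 58% | 95% |
| Underlying ability itself | 0.775 | 0.1079 | 67% | 89% | 54% | 93% |

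**Step 3: other assumptions.** Simulation with 1,000,000 draws per scenario took correlations with the underlying ability of 0.6 to 0.8 for the screen and 0.85 to 0.90 for the battery. Sensitivity runs from 47–62% at w = 0 to 52–67% at w = 0.1 and 64–76% at w = 0.3. Within a scenario the rise is 4 to 5 points at w = 0.1 and 13 to 17 points at w = 0.3. All four measures rise in every scenario. At w = 0 there is no incorporation effect.

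**The case against.** The strongest reply is that the authors plainly meant two separate things. Measurements (h) lists the assessment without the screens, and the sentence on staging follows that list. The analysis section sets screening tests against the neuropsychological evaluation, and the Discussion speaks of contrasting one with the other. Section 5 is a catalogue of instruments: it also contains the GDS, which is a result and not a test, so being listed there does not prove that a score feeds the stage. This stands in part. It shows that incorporation is a possibility and not an established fact. It does not close the gap, because no sentence excludes the screens and the operative analysis sentence uses the wider term.

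Two stronger readings are tempting. A reader might infer that whoever stages the participant has every score to hand. The article says only that staging follows evaluation. A reader might also infer that the screens are certain to look better than they truly are. The illustration does not show that. Against the underlying ability, sensitivity is 67%. A screen-free battery understates it (58%) because the battery is itself imperfect, a weight of 0.1 still understates it (63%), 0.2 is about equal (68%), and only 0.3 exceeds it (73%). What rises without exception is accuracy relative to a reference that leaves the screens out.

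Finally, withholding the scores on a separate sheet does not blind an examiner who has just administered the MMSE. That objection stands, and the fix allows for it.

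**Conclusion.** The point holds as a conditional one. As written, the reference standard may include the MMSE and 7 Minute Screen, or be assigned with knowledge of them. If so, all four accuracy measures will be higher than against an independent battery reference. The document does not support saying that this will happen, or that the reported figures must exceed the true accuracy.

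The size cannot be found from the document. Under the assumptions shown, sensitivity rises from about 58% to between 63% and 73% for screen weights of 0.1 to 0.3, and PPV from 47% to between 50% and 58%. The reliabilities, the weights and the 20% positive rate are all assumed.

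The issue is confined to objective 3. Using the screens in the staging would not be circular for the prevalence estimate or for the analysis of cardiovascular risk factors. It is still worth settling before staging begins, because a stage assigned with the scores in view can be made independent of them only by staging again.

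**What to change.** 1. In instrument section 5 (GDS entry) and in Statistical analysis, state that the reference classification for objective 3 rests on the tests from item (b) onward plus the Barthel index, the Lawton-Brody index and the IQCODE, and explicitly not on the MMSE or 7 Minute Screen. Name the tests instead of citing letters, because the lettering in section 5 is out of order and uses (h) twice.
2. Where existing staffing allows, record the GDS stage before the MMSE and 7 Minute Screen are totalled or entered.
3. If the same examiner both tests and stages, report incomplete blinding as a limitation. No additional rater is asked for.

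The cost is a short paragraph and a change in the order of data entry. If separation was already intended, one sentence saying so is enough for step 1. The downside is that the reported accuracy of the two screens may be lower.
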